### Randomization

Central randomization either to SECT or to EFST will control for random allocation to both interventions at each research site. For this purpose, an independent statistician developed randomization lists using a centrally computer-generated block-designed randomization procedure stratified by center. Only the principal investigator and his proxy have direct access to the randomization lists. Randomization results are directed at the local study manager.

### Blinding

Throughout the whole study, clinician raters are kept blinded. Results of the individual randomization process will be given only to the local study managers and the group therapists by the principal investigator. Study teams will be trained on how to avoid unblinding during the diagnostic process and team meetings. The statistician who will later analyze the results is as well kept blinded throughout the whole study.

### Intervention

The current study aims to compare two active psychotherapeutic group interventions, which are similar in their format and delivery. Groups include three to eight subjects who meet the outlined inclusion criteria. Each group will meet four times over a 4- to 5-month period for a full day of approximately 8 h on each occasion. All groups are led by purpose-trained, well-experienced psychological psychotherapists or psychotherapists in training on an advanced level (with a minimum of a bachelor’s and master’s degree in clinical psychology and ongoing clinical training). Psychotherapists are trained in both therapeutic interventions in the context of daylong workshops and using videotaped therapy roleplays. All therapists receive extensive feedback from the leading study center in Tübingen prior to delivering a study-relevant treatment group and, as such, are assessed in their competence to administer both interventions. To ensure the quality and coherence of the therapy groups throughout the study, therapists engage in monthly supervision and are required to send video recordings to the lead center for supervision purposes on an ongoing basis (following which written feedback is provided by telephone or email). In the following, the two conditions (i.e., intervention groups) are described in detail.

### Specific Emotional-Cognitive Therapy

The Specific Emotional-Cognitive Therapy (SECT; in German “Spezifische emotional-Kognitive Therapie” [SEKT]) is an innovative, cognitive-behavioral intervention comprising of four modules. Each of the four therapy days focuses on a particular module, which is delivered monthly in the style of a therapy workshop (from 9 am to 5 pm). SECT is a highly structured intervention, and module topics are designed based on their notable clinical relevance (see, for example, [15, 16]) and the empirical evidence base on psychological interventions for bipolar disorder [12, 17–20]. While mindfulness and acceptance (see below) are common interventions across each of the therapy days, the following four distinct modules are delivered across the 4 days, respectively:
Psychoeducation, structuring daily life, and life balanceRelative normality, detecting early warning signs of an episode, and interpersonal and problem-solving skillsCognitive and meta-cognitive skillsEmotion regulation skills

Each treatment day starts with mindfulness meditation, and consolidation of content from the previous therapy day’s content (including review of tasks to be completed at home, e.g., mood and activity diaries and skills development worksheets). The mood and activity diary, for example, is a record kept daily by participants to facilitate observation and learning in relation to mood change, behavior, thoughts, and daily events. Typically, this consistent component of the therapy day is concluded within the first 90 min, and is then followed by proceeding onto the relevant module for the day.

All treatment days are characterized by experiential exercises and the use of vignettes with worksheets and other materials targeting the unique needs of bipolar patients. Although SECT is a structured intervention, participants have an opportunity to work with personal examples relevant to the given topic of the day and are encouraged to exchange challenges and ideas. Therapists follow the common factors in the psychotherapy model proposed by Grawe [21], 2005 [22];. In addition, each patient will be provided with an informational and educational booklet pertaining to bipolar disorder and its treatment (roughly 30 pages in length).

### Emotion-Focused Supportive Therapy

The active control group, Emotion-Focused Supportive Therapy (EFST, in German “Emotionsfokussierte Supportive Therapie” [FEST]), is an interactional, self-help, support group. The concept of EFST was designed for this intervention study. The primary focus of EFST is to provide a platform for group members to exchange personal experiences, engage in self-reflection, express emotions, and provide mutual support. As in SECT, therapists follow the common factors in psychotherapy (Grawe [21], 2005 [22];. EFST therapists are empathetic, help patients to express emotions, give information, and reinforce patients in their self-help strategies and apparent resources. Patients are encouraged to interact with each other and to present opinions and current issues they are facing, as well as to ask one another about shared experiences and coping strategies adopted. In EFST, therapists do not structure meetings or the discussion, but rather facilitate and promote an atmosphere of supportive and friendly group discussion. EFST does not use material, exercises, or give homework such as keeping a mood or activity diary. For psychoeducational reason, each patient is provided with a small booklet about bipolar disorder (e.g., with definitions, statistics, and symptoms) and its pharmacological treatment; however, no specific psychological interventions are provided (e.g., cognitive-behavioral interventions).

### Assessments/measures

Four testing occasions will take place across this longitudinal study, with follow-ups at 5 to 6 months (i.e., immediately post-intervention) and again at 12 and 18 months post-baseline, whereby 18 months follow-up is the primary time point of interest. At baseline, participants’ bipolar disorder is diagnosed by using the Structured Clinical Interview for DSM-IV (structured clinical interview for DSM-IV, SCID 5, German version [23];) with a modified section to assess affective syndromes in line with DSM-V. Current episodes are assessed objectively and subjectively using the Young Mania Rating Scale (YMRS) [24], the Altman Self-Rating Mania Scale (ASRM) [25], and the Quick Inventory of Depressive Symptomatology clinician and self-report forms (QIDS-C, QIDS-SR) [26]. The Global Assessment of Functioning (GAF) [27] and Functional Assessment Short Test (FAST) [28] assess participants’ global social functioning. All measures are administered in the German language and are proven valid and reliable in the German version. The multiple-choice vocabulary intelligence test (“Mehrfachwahl-Wortschatz-Intelligenztest”; MWT) [29] is used as a measure of premorbid IQ. The Longitudinal Interval Follow-up Evaluation (LIFE) (DSM-IV version; developed by Keller et al. [30] and adapted in German for the current study, 2005) is additionally implemented as a key measure in assessing functioning and symptoms in bipolar disorder over time. Following the intervention, therapy satisfaction is assessed using nine items across a 4-point Likert scale using questions such as “The therapy I participated in was of a high quality.” Table 1 gives an overview of the assessment battery as implemented across measurement occasions.

**Table 1 Tab1:** Schedule of enrollment, interventions, and assessments

	Study period					
	First contact	Baseline/randomization	Intervention	Post-assessment	Follow-up 1	Follow -up 2
**Time point**	***Day 1***	***Days 1 to 28***	***Months 2 to 5***	***Months 5 to 6***	***Month 12***	***Month 18***
**Enrollment**						
**Eligibility screen**	X					
**Informed consent**		X				
**Randomization**		X				
**Interventions**						
***SECT***			X			
***EFST***			X			
**Assessments**						
***SCID***		X				
***LIFE***		X		X	X	X
***YMRS, QIDS-C***		X		X	X	X
***ASRM, QIDS-SR***		X		X	X	X
***GAF, FAST***		X		X	X	X
***MWT-B***		X				
***Therapy satisfaction***				X	X	

This template is in accordance with the Standard Protocol Items: Recommendations for Interventional Trials (SPIRIT) [31]

**Table 2 Tab2:** Ethical approval bodies and approval reference numbers at participating study sites

Ethics committee	Reference number
Eberhard Karls University Tübingen	235/2014BO1
Charité Berlin	EA1/105/17
Medical School Brandenburg, Neuruppin	Z-01-170614
University Hospital Carl Gustav Carus Dresden	EK 306072015
Ruhr University Hospital Bochum	15-5479
University Medical Center Hamburg-Eppendorf	MC-184/15
University Medical Centre Göttingen	29/2/16
Philipps University Marburg	Studie 30/15
Ludwig Maximilians University Munich	506-15
Goethe University Frankfurt	253/15

### Primary and secondary outcome measures

To examine the effect of the psychotherapy groups, the trial entails one primary outcome measure (relapse) and several secondary outcome measures: time to relapse (LIFE), relapse rate (LIFE), days missed at work/school (record, interview), and social functioning level [32].

Relapse is defined as the development of a new affective (either depression, [hypo] mania, or mixed) episode that meets the diagnostic criteria or results in a hospital admission. Relapse will be assessed every 6 months using the structured LIFE interview (at t2 [end of treatment], t3 [6 months after t2], and t4 [12 months after t2]). The LIFE leads to reliable information regarding the progression and course of illness, time in remission, development of new affective episodes (relapse), and also other mental disorders (co-morbidity). For example, patients are asked at t2, t3, and t4, “The last time we spoke you reported … [description of affective state at the time, e.g., ‘very depressed with problems sleeping’] … How has it been since then? … Since when have you been feeling better/worse?” This is followed with a formal rating based on DSM criteria (“Psychiatric Status Rating”) making note of when the change occurred (“Change Points”) leading to the collection of weekly ratings for the episode. Patients are encouraged to be specific regarding the changes. The interviewer facilitates this by asking questions such as “Was that in November?” and “Did that happen before or after the holiday season?”

Measurements of symptomatology (QIDS-C/SR, YMRS, ASRM), social functioning, and quality of life are assessed to integrate the patient’s everyday perspective (FAST).

Assessment of these outcomes as indicated by changes in these measures over time allows us to address our main hypotheses, i.e., whether SECT versus EFST shows reduced relapse rates, less missed days from work/school, less days spent in the hospital, lower health costs, improved treatment compliance, higher social functioning, and improved neurobiological functioning.

### Sample size calculation

Sample size calculations refer to a log-rank statistic under *α* = 0.05 and *β* = 0.2 (80% power) under the assumptions of (a) an accrual time of 24 months, (b) a total study duration of 48 months with a primary time point of interest at 18 months post-baseline, and (c) a drop-out rate of 12% (the latter based on experiences from previous studies [2, 3, 5]; and relates to the study observation period of 18 months). We define a treatment effect of factor 2 as a relevant effect, i.e., a hazard ratio (HR) of 0.5, for instance, is regarded as a relevant effect. Previous trials have indicated about 4% of the study population under risk (excluding dropouts) will experience a relapse under conventional therapy each month. HR = 0.5 would require 2% per month for the SECT group and a study population of *N* = 360 patients (180 patients per treatment arm) to reach significance under *α* = 0.05 and *β* = 0.2. The study with a proposed *N* = 300 would require HR = 0.46, and the pessimistic scenario of *N* = 200 would have to reach HR = 0.375. Thus, the study with *N* = 300 intended can yield statistical significance if the treatment effect in the SECT group exceeds factor 2. In addition, our sample size calculation is based on the publication by Jahn-Eimermacher et al. [33] which fits—regarding sample sizes for time-to-event data—the requirements of the present study best and results in an identical sample size.

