### Statistical analysis

The question as to whether specific psychotherapy can prolong the time until relapse will be addressed by non-parametric survival analyses involving log-rank or Wilcoxon statistics and sensitivity analyses for the ITT (intent-to-treat) sample and the PP (per-protocol, required is participating in at least 75% of treatment sessions) sample. The time-dependent evolution of group-specific hazard rates will be investigated by parametric models addressing the differences in the dynamics of relapse in both intervention arms. Cox regressions will be performed to identify the risk factors for the probability of relapse and time until relapse if the proportional hazard assumption will not be negated. Our planned analyses will allow to identify if the types of participants with missing outcomes look different to those observed outcomes and whether this pattern might be different by arm: treatment arm with no missing primary outcome at primary time point, treatment arm with missing primary outcome at primary time point, control arm with no missing primary outcome at primary time point, and control arm with missing primary outcome at primary time point. Secondary endpoints like symptomatology, days missed at work/school, or social functioning level will be described on a univariate level and enter multivariable group comparisons on the base of an ANCOVA (with the factor kind of intervention (2) and time points (2 to 4) using baseline as a covariate) and involve stepwise variable selection. Based on the results for these covariates, methods such as principal component analysis or latent variable modeling will finally be considered to identify the risk factors for the probability of relapse and time until relapse. We have the intention to use the CONSORT statement for reporting the outcome and final results of this randomized controlled trial.

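### The plan allows a Wilcoxon test although therapy starts after baseline; under a delayed effect that test loses power against the log-rank test on which the trial was sized.

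*Protocol article*

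**What the plan says.** All references are to the protocol article.

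- **Sample size calculation.** The basis is a "log-rank statistic under *α* = 0.05 and *β* = 0.2 (80% power" with 18 months post-baseline as the primary time point and 12% dropout over that period. The control rate is given as "about 4% of the study population under risk (excluding dropouts) will experience a relapse under conventional therapy each month". On effect size, "a hazard ratio (HR) of 0.5, for instance, is regarded as a relevant effect", and for the intervention arm "HR = 0.5 would require 2% per month for the SECT group". This leads to "360 patients (180 patients per treatment arm"; the planned N=300 is said to require HR 0.46. No delay before the effect starts is mentioned.
- **Intervention.** "Each group will meet four times over a 4- to 5-month period". Table 1 puts therapy in months 2 to 5, after a baseline and randomization column covering days 1 to 28. Under Design and procedure, patients join the next possible meeting of a slow-open group.
- **Primary and secondary outcome measures.** The LIFE interview at t2 rates the whole interval since the previous contact, so relapses before the first therapy day are captured. No section excludes them.
- **Statistical analysis.** Time to relapse is compared by "log-rank or Wilcoxon statistics", with no choice between the two. Parametric models are planned for hazards that change over time, and Cox regression for risk factors "if the proportional hazard assumption will not be negated".

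**The concern.** Both arms continue routine psychiatric care, and nothing in the group programmes can separate them before the first group day. SECT then delivers its four modules at monthly intervals, so a gradual build-up is more plausible than a halved hazard from time zero. Relapses in the early weeks therefore carry little or no information about the treatment difference.

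A Wilcoxon test weights each relapse by the number still at risk, so it gives those early events the most weight. If Wilcoxon became the primary test, the trial would lose power under the pattern its own schedule makes likely, and would use a test other than the one it was sized on. Leaving the choice open also allows it to be made late.

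**Working it through.** **1. The plan's own figure.** Inputs from the sample size section: 4% per month in controls, HR 0.5, 18 months, 12% dropout, 80% power; two-sided 5% is assumed because sidedness is not stated.
- Events (Schoenfeld): 4 × (1.960 + 0.842)² / (ln 0.5)² = 4 × 7.85 / 0.480 = 65.4, so 66.
- Relapse by month 18: control 1 − 0.96^18 = 0.520; SECT 1 − 0.96^9 = 0.307; mean 0.414.
- N = 66 / 0.414 / 0.88 = 181.2, so 182 in total. The document states 360.
- For HR 0.46: 53 events, mean probability 0.404, N = 53 / 0.404 / 0.88 = 149.1, so 150. The document states 300.

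The stated totals are about twice what these inputs need. Why is a separate question, but it means that under a constant HR of 0.46, N=300 has about 98% power rather than 80%. That surplus absorbs much of any delay.

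**2. How many relapses fall early.** At 4% per month, the share of 18-month control relapses in month 1 is 0.04 / 0.520 = 8%. The share by month 5 is (1 − 0.96^5) / (1 − 0.96^18) = 0.185 / 0.520 = 36%.

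**3. How the two tests weight time.** Relative Gehan-Wilcoxon weight per event is 1.00 at month 0, 0.96 at month 1, 0.93 at month 2 and 0.80 at month 6. Share of total weight:

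| Period | Wilcoxon | Log-rank |
|---|---|---|
| First month | 10% | 8% |
| First two months | 19% | 15% |
| First five months | 43% | 35% |

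**4. Power under delayed onset.** Simulated trials with 150 per arm and 18 months of follow-up: control hazard −ln(0.96) per month, dropout hazard −ln(0.88)/18, two-sided 5%. In the ramps the log hazard ratio falls linearly to its full value. The documents give no onset shape, so a range is shown.

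| Onset of effect, N=300, HR 0.46 | Log-rank | Wilcoxon | Loss (points) |
|---|---|---|---|
| Constant from baseline | 98% | 98% | 0 |
| None in month 1, then full | 96% | 94% | 2 |
| Ramp over months 1 to 5 | 86% | 79% | 7 |
| Ramp over months 2 to 5 | 83% | 73% | 10 |
| None until month 5, then full | 69% | 52% | 17 |

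Repeat runs differ by one or two points. At HR 0.5, which the plan calls relevant, N=300 gives 91% and 89% (one-month lag), 78% and 69% (ramp 1 to 5), 75% and 63% (ramp 2 to 5), and 60% and 45% (none until month 5). The document does not say which Wilcoxon version is meant. The Peto-Prentice form loses a little less than Gehan: 71% rather than 69% in the ramp 1 to 5 case at HR 0.5.

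**5. The opposite pattern.** If the effect starts at month 1 and is lost after month 12 (HR 0.5, N=300), Wilcoxon has about 69% power and log-rank about 63%.

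**The case against.** Four points can be made for the plan.

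- *The delay may be short.* In Table 1, day 1 is first contact and randomization may fall as late as day 28, so some patients could start within days. A full untreated month after randomization is towards the upper end of the table's schedule, although the wait for the next group meeting could lengthen it. The time origin of the survival analysis is inferred from the 18-month time point and the LIFE intervals; it is not stated. This stands, and is why the lag is treated as an assumption.
- *The planned power largely survives.* A reader might infer that the constant hazard ratio invalidates the 80% power. The documents do not support that. A halved hazard is ruled out only before therapy starts, 0.5 can be read as an average effect, and at N=300 and HR 0.46 log-rank keeps at least 80% power with a ramp over months 1 to 5 or 2 to 5. This rests on the unexplained surplus in N: with 180 patients in total and HR 0.5, log-rank power is 82% under a constant effect but 75% with a one-month lag.
- *Changing hazards are foreseen.* A reader might infer that rejecting proportional hazards would leave a p-value with no effect size. The analysis section plans parametric models for time-dependent hazards in each arm and assigns Cox regression to risk factors, so that inference fails.
- *Wilcoxon is not always worse.* It gains if the benefit fades late. This stands as a real trade-off, but the section gives no such reason for keeping both tests.

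**Conclusion.** The point holds in a limited form. The schedule makes a delayed effect likely, the sample size section does not mention it, and the permitted Wilcoxon test is the weaker choice under that pattern. At N=300 and HR 0.46 the loss is about 2 to 17 points. With a ramp over months 1 to 5 or 2 to 5, Wilcoxon falls below 80% where log-rank stays above it. Log-rank itself falls clearly below 80% at HR 0.46 only if there is no effect until about month 5; at HR 0.5 it is already at 78% with a ramp over months 1 to 5.

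It would go too far to say that Wilcoxon rests mainly on the untreated months. That is true per event only: the first two months carry 19% of its total weight, against 15% for log-rank.

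The size depends on the assumed onset shape, two-sided 5% testing, time counted from about randomization, and the stated 4% monthly rate and 12% dropout.

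**What to change.** In Statistical analysis, remove Wilcoxon as an option for the primary intention-to-treat comparison. Name the log-rank test, on which the sample size rests, as the single primary test, with time counted from randomization. Report the Kaplan-Meier difference in relapse-free proportion at month 18 with a 95% CI whatever the proportional-hazards check shows; restricted mean time to relapse is an optional addition.

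In Sample size calculation, say that the hazard ratio is an assumed constant effect from baseline, and give power under at least one stated lag.

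The cost is wording and a short calculation. The price in power is about 6 points (69% against 63%) if the effect is lost after month 12. A late-weighted Fleming-Harrington test may be added as a sensitivity analysis but is not needed; it bets on a late effect just as Wilcoxon bets on an early one.

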### Statistical analysis

The question as to whether specific psychotherapy can prolong the time until relapse will be addressed by non-parametric survival analyses involving log-rank or Wilcoxon statistics and sensitivity analyses for the ITT (intent-to-treat) sample and the PP (per-protocol, required is participating in at least 75% of treatment sessions) sample. The time-dependent evolution of group-specific hazard rates will be investigated by parametric models addressing the differences in the dynamics of relapse in both intervention arms. Cox regressions will be performed to identify the risk factors for the probability of relapse and time until relapse if the proportional hazard assumption will not be negated. Our planned analyses will allow to identify if the types of participants with missing outcomes look different to those observed outcomes and whether this pattern might be different by arm: treatment arm with no missing primary outcome at primary time point, treatment arm with missing primary outcome at primary time point, control arm with no missing primary outcome at primary time point, and control arm with missing primary outcome at primary time point. Secondary endpoints like symptomatology, days missed at work/school, or social functioning level will be described on a univariate level and enter multivariable group comparisons on the base of an ANCOVA (with the factor kind of intervention (2) and time points (2 to 4) using baseline as a covariate) and involve stepwise variable selection. Based on the results for these covariates, methods such as principal component analysis or latent variable modeling will finally be considered to identify the risk factors for the probability of relapse and time until relapse. We have the intention to use the CONSORT statement for reporting the outcome and final results of this randomized controlled trial.

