### Design and procedure

This psychotherapy study is designed as a parallel-group, individually randomized controlled trial (RCT) with blind assessment raters. Patients are screened at baseline (t1) by trained diagnostic clinicians (clinical psychologists or psychiatrists) and enrolled giving their informed consent to the study protocol and meeting full inclusion criteria. Patients are then individually randomized to one of the respective treatment groups. Patients will be immediately informed via phone call about the randomization result by the group therapist they are located to. The group therapist will invite the patient to the next possible group meeting. Groups are ongoing, slow-open groups, admitting new participants when someone is terminated. The intervention takes place over up to 5 months between t1 and t2 and is delivered in four full therapy days of approximately 8 h in small groups up to eight subjects. Patients are then seen at the end of treatment (t2 at month 6) and twice during follow-up (t3 at month 12; t4 at month 18). The flowchart (see Fig. 1) visualizes the study steps.

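### Both therapies are given in slow-open groups of three to eight, but the test named for time to relapse treats patients as independent; if outcomes correlate within groups, its type I error exceeds 5%

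*Protocol article*

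**What the plan says.** The Design and procedure section describes a "parallel-group, individually randomized controlled trial (RCT) with blind assessment raters". The Intervention section sets out to "compare two active psychotherapeutic group interventions, which are similar in their format and delivery", and adds: "Groups include three to eight subjects who meet the outlined inclusion criteria". Each group meets for four full days over four to five months. Membership rolls over time: "Groups are ongoing, slow-open groups, admitting new participants when someone is terminated" (Design and procedure).

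Under Statistical analysis, the question whether the specific therapy prolongs time to relapse "will be addressed by non-parametric survival analyses involving log-rank or Wilcoxon statistics". The Sample size calculation section also rests on a log-rank statistic. Neither section, nor Additional analyses, mentions therapy group, therapist, frailty or a robust variance. The intraclass correlations under Additional analyses concern agreement between raters. The Discussion concedes that the group setting and variation in group size may influence outcome, but lists these as limitations and attaches no analysis to them.

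**The concern.** Patients in one group share sessions, leaders and peers. In the control therapy, exchange and support among members is the main ingredient. Outcomes within a group may therefore be alike. Individual randomisation does not remove this, because the likeness arises after allocation and each group lies wholly in one arm. With positive within-group correlation, the ordinary log-rank or Wilcoxon variance is too small, confidence intervals are too narrow and false positives are too frequent.

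At stake is the trial's main claim, that specific content beats support. An unadjusted test can mistake a few favourable groups for that effect.

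**Working it through.** **Inputs from the article.** Groups of 3 to 8; 10 centres; planned N = 300; 18 months of follow-up; 12% drop-out; α = 0.05 (sidedness not stated, two-sided assumed); 80% power. For the control rate, "about 4% of the study population under risk (excluding dropouts) will experience a relapse under conventional therapy each month". For the effect, "a hazard ratio (HR) of 0.5, for instance, is regarded as a relevant effect".

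**Assumed.** The within-group ICC is not given; the range used is 0.01 to 0.10.

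**1. The plan's own sample size.**
- Events for HR 0.5: 4 × (1.96 + 0.84)² / (ln 0.5)², rounded up to 66.
- With monthly hazard −ln(0.96), 18-month relapse probabilities are 0.520 (control) and 0.307 (HR 0.5), mean 0.414.
- N = 66 / 0.414 / 0.88, about 182 in total.

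The article states 360. Twice the recomputed figure is 364. HR 0.46 and HR 0.375 behave the same way: 150 and 99 recomputed, against 300 and 200 stated. The stated numbers therefore look like totals read as per-arm figures, but the article does not say so, and that is a separate matter. It bears on this point only because it leaves power in reserve.

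**2. Type I error by formula.** Design effect DE = 1 + (m − 1) × ICC; true size = 2 × [1 − Φ(1.96 / √DE)]. Example with m = 8 and ICC = 0.05: DE = 1 + 7 × 0.05 = 1.35; 1.96 / √1.35 = 1.687; size 9.2%.

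| Patients per group | ICC 0.01 | ICC 0.02 | ICC 0.05 | ICC 0.10 |
|---|---|---|---|---|
| 3 | 5.2% | 5.5% | 6.2% | 7.4% |
| 5.5 | 5.5% | 6.0% | 7.7% | 10.4% |
| 8 | 5.8% | 6.6% | 9.2% | 13.3% |

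DE runs from 1.02 to 1.70, so 300 patients carry the information of about 294 (300 / 1.02) down to 176 (300 / 1.70) independent patients.

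**3. Check by simulation.** Null trials of about 300 patients were simulated with exponential relapse times, a gamma frailty shared within groups nested in arm, 18 months and 12% drop-out, 8,000 runs per cell. Frailty variances of 0.05, 0.1 and 0.25 correspond to 18-month ICCs of about 0.02, 0.05 and 0.11.

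| Patients per group | No group effect | ICC about 0.02 | ICC about 0.05 | ICC about 0.11 |
|---|---|---|---|---|
| 3 | 4.9% | 5.0% | 5.7% | 7.3% |
| 5 | 5.2% | 6.5% | 7.5% | 9.9% |
| 8 | 4.9% | 7.2% | 9.0% | 14.1% |

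With a variance clustered on therapy group, simulated size was 4.2% to 5.0% in every cell.

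**4. Rolling membership.** 300 / (10 centres × 2 arms) = 15 patients per centre and arm. If all 15 shared one effect, simulated size (3,000 runs) was about 10% at ICC 0.02 and 13% at ICC 0.05.

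**5. Power at N = 300, HR 0.5.** Expected events are 300 × 0.88 × 0.414 = 109. Dividing events by DE gives power of 95% (DE 1), 93% (1.10), 88% (1.35) and 79% (1.70).

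**The case against.** The strongest reply is that the inflation is hypothetical. No within-group correlation is given, and at ICC 0 the ordinary test has its nominal size. For three per group with ICC up to 0.02, the excess is about half a percentage point. This stands, and it limits the claim.

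Second, other features can offset the inflation. Therapists are trained and certified in both therapies, so where one therapist leads both arms the therapist effect is crossed with treatment. Randomisation is stratified by centre, and an unstratified log-rank is then somewhat conservative. With an added centre frailty variance of 0.1, simulated size was about 4.7% to 4.9% for three to five per group at ICC 0.02. This also stands, but at eight per group or higher ICC the offset did not restore 5%. A reader might infer that therapist effects necessarily add to the error. The article does not say whether individual therapists ran one arm or both.

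Third, a reader might take the 15-per-line figures as the expected case. They are an upper bound. Each patient attends four days over four to five months, while recruitment runs from August 2015 to December 2019, so early and late members of one line never meet.

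Fourth, this is a condensed article, and a separate analysis plan could specify a clustered version of the test. That is possible. But the article names the test and bases the sample size on the same statistic without any group term, so the point concerns a stated choice and not only missing detail.

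Finally, a reader might infer that the sample size definitely assumes independent patients. The article also cites a published time-to-event method whose assumptions are not visible here, so this cannot be asserted.

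**Conclusion.** The point holds in conditional form. Groups are nested within arm, and the named test does not account for them. If within-group correlation is positive, the standard error is too small. For an assumed ICC of 0.01 to 0.10, the formula gives a true type I error of about 5.2% to 7.4% with three per group and 5.8% to 13.3% with eight. It is practically nominal at the low end, and higher if the effective cluster exceeds eight.

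The article does not support the unconditional statement that the type I error exceeds 5%, because it gives no correlation. Nor does it support reading this as a shortage of patients: on the recomputed inputs, power at HR 0.5 falls to about 79% only at a design effect of 1.70. The concern is mainly false positives. All figures assume a two-sided test, equal group sizes and the assumed ICC range.

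**What to change.** Keep time to first relapse as the endpoint. Base the primary test and confidence interval on a log-rank (Cox score) test with a small-sample-corrected variance clustered on therapy group, stratified by centre as randomised. This need not turn the primary comparison into a model-based one. A shared frailty for therapy group can serve as a sensitivity analysis.

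Record group and therapist identifiers for each session. Fix in advance a rule that assigns each patient to one group, for example the group of first attendance, with the whole centre-by-arm line as the cluster in a sensitivity analysis. That analysis has only 20 clusters (10 centres × 2 arms), so the small-sample correction matters most there. Treat therapist as crossed with arm wherever one therapist led both.

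The cost is a change of analysis wording, retention of the identifiers, some loss of power as shown above, and wider intervals. On the log hazard ratio scale the width grows by √DE: about 1% at DE 1.02, 16% at 1.35 and 30% at 1.70. Identifiers not kept during the trial may be hard to reconstruct later.
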